## Objectives

### Primary endpoint

Overall survival: defined as time from enrollment to death from any cause

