## Statistical considerations

### Statistical design and sample size

The primary endpoint of this study is overall survival in patients able to be treated with a dose of 50 Gy in 5 fractions, with a comparison to historical controls of untreated medically inoperable patients stage I NSCLC, which consistently have survivals of less than 1 year, as described in the Background section. Demonstration in this study that median OS after SABR is statistically greater than a historical control of < 12 months would indicate that SABR is worthwhile in this population of ILD patients, if toxicity is within acceptable limits.

A sample size of 39 patients provides >80% power to detect an OS improvement of >20% at 1 year, compared to a historical control of <50% (i.e. 70% vs. 49%), using a one-sample, one sided binomial test at the 0.05 significance level, assuming 10% dropout or loss to follow-up before one year. All cohorts will be combined for this primary analysis.

SABR will be considered worthwhile if OS is > 1 year, the risk of grade 3 or 4 pulmonary toxicity is < 35%, and the risk of treatment-related mortality is < 15%.

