### Data safety monitoring

The DSMC will meet every 6 months after study initiation to review toxicity outcomes, but will also be notified in-between meetings if more than 2 grade 5 treatment-related toxicities occur within the first 7 patients enrolled to any cohort, or for any subtype of ILD regardless of cohort.

The dose will be de-escalated if 2 or more of the first 7 patients in a specific cohort or with a specific ILD subtype experience grade 5 treatment-related toxicity within 6 months of treatment. For example, if 2 of the first 7 patients in cohort III experience grade 5 toxicity within 6 months of treatment, then the dose will be de-escalated for all future patients in cohort III. Similarly, if 2 of the first 7 patients with CTD-ILD experience grade 5 toxicity within 6 months of treatment, then the dose will be de-escalated for all future patients with CTD-ILD.

After each de-escalation, if 2 of the next 7 patients in that cohort develop grade 5 toxicity within 6 months of treatment, then de-escalation will be repeated. The dose will be de-escalated to 50 Gy in 10 fractions, then 45 Gy in 15 fractions, using the same dose prescription techniques as described above. After 45 Gy in 15 fractions, if further de-escalation is needed then that cohort will be closed.

Using binomial distribution modelling, the performance characteristics of this approach are displayed in Table 6.

**Table 6 Tab6:** Probability of dose de-escalation based on true risk of death in a given patient cohort

True Risk of Death in a Given Cohort	Probability of De-Escalation for that Cohort
0.08	10%
0.15	28%
0.30	67%

^a^At risk levels higher than 30%, which are thought to be extremely unlikely, dose de-escalation probabilities rise further, and chances of de-escalation within the first few patients are very high

If de-escalation occurs for a certain cohort, then further patients enrolled in that cohort will be treated with de-escalated doses but will not count towards the overall accrual goal (i.e. there will be 39 patients treated with 50 Gy in 5 fractions, although ALL patients treated will be followed for outcomes and reported). Final results will be stratified by dose level: they will be presented for all patients, patients treated with the target dose of 50 Gy in 5 fractions, and for patients treated at de-escalated doses.

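### The stated power above 80% is about 77% for the named binomial test once the protocol's own 10% dropout is applied

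*Protocol article*

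**What the plan says.** All the planning inputs are in one paragraph of the protocol article, under Statistical design and sample size:

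- Size and power: "A sample size of 39 patients provides >80% power to detect an OS improvement of >20% at 1 year".
- Null and alternative 1-year survival, 49% and 70%: "compared to a historical control of <50% (i.e. 70% vs. 49"%).
- Test: "using a one-sample, one sided binomial test at the 0.05 significance level".
- Attrition: "assuming 10% dropout or loss to follow-up before one year".
- Analysis set: "All cohorts will be combined for this primary analysis".

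Data safety monitoring confirms that the accrual goal refers to the target dose: "there will be 39 patients treated with 50 Gy in 5 fractions". Under Primary endpoint, overall survival is "defined as time from enrollment to death from any cause".

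The paragraph does not call the test exact, gives no critical number of survivors, and does not say how patients lost before one year enter the analysis.

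**The concern.** This sentence is the only justification given for the sample size. It fixes the null, the alternative, the sidedness, the alpha and the dropout, so its power figure can be checked without outside information. The figure does not follow from those inputs for the test that is named.

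What is at stake is limited. If 1-year survival really is 70%, the chance that the trial misses it is about 23%, whereas the text promises less than 20%. Without a critical count, a reader also cannot see which result would count as success on the primary endpoint.

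**Working it through.** **Inputs** (all from Statistical design and sample size): N = 39, p0 = 0.49, p1 = 0.70, one-sided alpha 0.05, dropout 10%.

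**Evaluable patients.** 39 × 0.90 = 35.1, so about 35.

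**Reproducing the protocol's figure.** The usual large-sample formula with null variance is

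power = Φ{ [p1 − p0 − 1.645 √(p0(1 − p0)/n)] / √(p1(1 − p1)/n) }.

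At n = 35:

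- √(0.49 × 0.51/35) = 0.0845, and 1.645 × 0.0845 = 0.1390.
- √(0.70 × 0.30/35) = 0.0775.
- (0.21 − 0.1390)/0.0775 ≈ 0.917, and Φ(0.917) = 0.820.

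This gives 82.0%. An arcsine formula gives 81.8%. A power above 80% with 39 enrolled is therefore what a standard planning formula returns. With continuity correction the same formula gives 76.8%.

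**What the named test does at n = 35.** Take the smallest r with P(X ≥ r | 35, 0.49) ≤ 0.05, then compute P(X ≥ r | 35, 0.70).

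| Reject if at least | True alpha at 0.49 | Power at 0.70 |
|---|---|---|
| 22 of 35 | 0.0703 | 86.5% |
| 23 of 35 | 0.0347 | **77.3%** |

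A cut-off of 22 breaks the 0.05 limit, so the cut-off is 23.

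**Does it matter that the text does not say exact?** Not at n = 35. For 22 survivors the score statistic is (22/35 − 0.49)/0.0845 = 1.640, just under 1.645. The large-sample score test therefore also needs 23 survivors, as does a mid-P rule. Both have the same true power, 77.3%. The 82.0% is a smooth approximation and not the rejection probability of either test.

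**Sensitivity to the number evaluable** (exact rule, p0 = 0.49, p1 = 0.70):

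| Evaluable | Cut-off | Alpha | Power |
|---|---|---|---|
| 33 | 22 | 0.0311 | 73.3% |
| 34 | 22 | 0.0479 | 80.7% |
| 35 | 23 | 0.0347 | 77.3% |
| 36 | 24 | 0.0248 | 73.7% |
| 37 | 24 | 0.0382 | 80.7% |
| 38 | 25 | 0.0277 | 77.5% |
| 39 (no dropout) | 25 | 0.0417 | 83.7% |

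The number lost cannot be chosen. Weighting these powers by a Binomial(39, 0.9) number evaluable gives 77.0%. Exact power is at or above 80% for every n only from 39 evaluable upward. At 10% loss that means 39/0.9 = 43.3, so 44 enrolled.

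**Time-to-event alternative.** I simulated 39 patients with exponential survival, 10% random censoring by 12 months and follow-up cut at 12 months (20,000 replicates):

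- Kaplan-Meier 12-month survival with a log-log one-sided 95% lower bound against 0.49: power 80.7%, type I error 3.9%.
- One-sample log-rank test against 49% at 12 months: power 81.9%, type I error 3.8%.

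Exponential survival and random censoring are assumptions of this check. The protocol does not state them.

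**The case against.** The strongest defence is that the figure is an ordinary planning calculation. The large-sample formula reaches 80% at 34 evaluable patients, which is 34/0.9 = 37.8, so 38 enrolled. A search for the smallest n with exact power above 80% also stops at 34. Both fit within 39. The gap at 35 is 2.7 points on a sawtooth curve, and an alternative of 71% with a null of 50% would give 81.1% at 35. The target is also worded loosely, with inequalities around both the control rate and the improvement.

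Most of this stands as an explanation of where the figure came from, and as a reason to treat the point as small. It does not make the sentence correct. The protocol gives 70% and 49% as its worked values and 10% as its dropout. At those values the test, exact or score, has 77.3% power.

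A reader might infer more than the document supports:

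- That patients lost before 12 months will be discarded, or counted as dead, and that informative dropout will therefore bias the result. The protocol mentions dropout only as a sample-size assumption and defines survival as a time to event. How losses are handled is not stated, and is commonly left to the analysis plan.
- That power could be near 51.5%, which is what counting every lost patient as not alive would give (39 patients, cut-off 25, success probability 0.70 × 0.90 = 0.63). The protocol adopts no such rule.
- That a power above 80% can arise only by approximation or by ignoring dropout. Exact power is 80.7% at 34 and at 37 evaluable.

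**Conclusion.** The power statement is wrong as written, by a small amount. With 35 evaluable patients the named test has 77.3% power, and 77.0% averaged over random 10% dropout, against a stated figure above 80%. This rests only on the protocol's own inputs and on reading 10% dropout as about 35 patients with known 1-year status.

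It is a modest overstatement that comes from discreteness, not a failed design. At a cut-off of 23 of 35 the type I error is 0.035, so the false-positive rate is protected. A binomial test on a 1-year proportion is an accepted way to size a single-arm phase II trial, so nothing here requires a different primary test.

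**What to change.** Restate the power as about 77% with 35 evaluable patients, and give the decision rule: reject at 23 or more of 35 alive at one year, attained alpha 0.035. State that the calculation is exact. This costs one sentence and no patients, and the quoted power becomes slightly less favourable.

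Two optional alternatives would support a figure of at least 80%:

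- Analyse all 39 patients with a one-sample time-to-event method, either a Kaplan-Meier 12-month lower bound against 0.49 or a one-sample log-rank test. This matches the endpoint definition and needs no extra enrolment. Its power, roughly 80% to 82% in the check above, must be stated together with the survival and censoring assumptions behind it. The Kaplan-Meier version only just clears 80%.
- Keep the binomial test and raise enrolment at the target dose to 44, five more patients.

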### Interstitial lung disease and SABR

Interstitial lung disease (ILD), also known as diffuse parenchymal lung disease, comprises a heterogeneous group of diseases characterized by a non-neoplastic, diffuse inflammatory and/or fibrotic pathology affecting the lung parenchyma, usually exhibiting a restrictive defect on pulmonary function testing with reduced gas exchange [7, 8].

ILD can be subdivided into fibrotic and non-fibrotic subtypes. Fibrotic subtypes include idiopathic pulmonary fibrosis (IPF), connective tissue disease-associated ILD (CTD-ILD), idiopathic non-specific interstitial pneumonia, hypersensitivity pneumonitis, and unclassifiable ILD. Fibrotic ILDs are characterized by reticulation, traction bronchiectasis, and frequently honeycombing on high-resolution computed tomography (HRCT). These fibrotic subtypes of ILD are the focus on this research protocol.

Patients with NSCLC and co-existing fibrotic ILD represent a high-risk group for any type of cancer treatment. Patients with ILD and NSCLC are at risk of both treatment-related toxicities and acute exacerbation of ILD [9], which can be life-threatening and even fatal. Despite the generally favorable toxicity profile of SABR, emerging data indicate that patients with pre-existing ILD are at particularly high risk of toxicity after SABR. A recent meta-analysis examined outcomes after several different treatments for early-stage lung cancer in patients with ILD [10]. Within the meta-analysis, 13 published studies (Additional file 1) assessed outcomes after SABR. Overall, the use of SABR in patients with early-stage NSCLC and pre-existing ILD was associated with a 25% risk of radiation pneumonitis (grade 3 or higher) and a 15% risk of treatment-related death. The risk may be highest in the subset of patients with IPF: SABR-related mortality was 33% in studies limited to IPF patients, and 14% in other studies that included only non-IPF fibrotic ILD, or a combination of IPF and non-IPF fibrotic ILD patients (*p* = 0.092).

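### A single mortality limit and one conclusion for all ILD patients leave a cohort or subtype taken off 50 Gy in 5 fractions nominally inside the "worthwhile" claim

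*Protocol article*

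**What the plan says.** Under Statistical design and sample size, the analysis population is set by "The primary endpoint of this study is overall survival in patients able to be treated with a dose of 50 Gy in 5 fractions", and the survival paragraph ends with "All cohorts will be combined for this primary analysis". A favourable survival result "would indicate that SABR is worthwhile in this population of ILD patients, if toxicity is within acceptable limits". The limits follow in one sentence: survival beyond 1 year, grade 3 or 4 pulmonary toxicity under 35%, and "the risk of treatment-related mortality is < 15" percent. The same limits appear under Rationale for primary endpoint and study design. Neither section says which patients form the denominator of the toxicity limits.

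Data safety monitoring judges the same harm group by group: "The dose will be de-escalated if 2 or more of the first 7 patients in a specific cohort or with a specific ILD subtype" have grade 5 treatment-related toxicity within 6 months. After that, "further patients enrolled in that cohort will be treated with de-escalated doses but will not count towards the overall accrual goal", so that "there will be 39 patients treated with 50 Gy in 5 fractions".

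Separate presentation is mentioned in three places. Data safety monitoring stratifies final results by dose level, the Fig. 1 legend stratifies the analysis by ILD severity, and Authorship allows separate cohort reports. None of these is tied to the decision rule.

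**The concern.** The plan has two rules for treatment-related death, and they work on different units. The de-escalation rule acts on a cohort or subtype. The final rule gives one answer for everyone.

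Once a group triggers, its later patients no longer enter the 39, and their places go to groups that have not triggered. The pooled rate is therefore pulled towards the rate in the remaining groups. No passage then limits the conclusion to those groups. Followed as written, the plan can take a group off 50 Gy in 5 fractions because of deaths and still report that treatment as worthwhile for a population that includes the group.

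The protocol itself expects risk to differ. Under Interstitial lung disease and SABR, "SABR-related mortality was 33% in studies limited to IPF patients", against 14% in the other studies. Under ILD severity, it hypothesises that subtype and lung function affect radiation toxicity. What is at stake is the scope of a safety conclusion about a possibly fatal toxicity. The type I error and power of the survival test are not affected.

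**Working it through.** **Inputs from the protocol article.** Trigger: 2 or more deaths in the first 7 of a cohort or subtype. Number at 50 Gy in 5 fractions: 39. Mortality limit: below 15%. Cited mortality: 33% in IPF-only studies, 14% in the others.

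**1. The plan's own figure.** P(trigger) = 1 − (1−p)^7 − 7p(1−p)^6. At p = 0.08, 0.15 and 0.30 this gives 10.3%, 28.3% and 67.1%, which matches Table 6 (10%, 28%, 67%). At p = 0.33 it gives 73%.

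**2. What the pooled limit allows.** 5/39 = 12.8% passes and 6/39 = 15.4% fails, so up to 5 deaths are allowed. A group stopped at 2/7 (28.6%) leaves room for 3 deaths in the other 32: 2/7 + 3/32 = 5/39. A group stopped at 3/7 leaves room for 2.

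**3. Chance that the pooled rate passes after one group has triggered.** This is P(X ≤ 3) after 2/7, or P(X ≤ 2) after 3/7, with X binomial on 32 patients. The risk in those 32 is an assumption.

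| Risk in the other 32 | After 2/7 | After 3/7 |
|---|---|---|
| 5% | 93% | 79% |
| 8% | 75% | 52% |
| 10% | 60% | 37% |
| 15% | 27% | 12% |

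**4. Simulation of the whole rule.** The assumptions are:
- three cohorts and five subtypes, assigned independently;
- IPF risk 33%, and one common risk in all other subtypes;
- 20-60% of patients with IPF;
- outcomes known at once;
- a group leaves the dose at its second death within its first 7;
- accrual until 39 have had 50 Gy in 5 fractions, with a pass at 5 or fewer deaths.

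IPF is de-escalated in about 67-74% of trials. Among those trials:

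| Risk in other subtypes | Pooled limit still passes |
|---|---|
| 5% | about 90% |
| 8% | about 70% |
| 10% | about 55% |
| 14% | about 26% |

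As a share of all trials, IPF de-escalated and limit passed together occur in about 16-66%. The low end belongs to the 14% risk.

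The timing of the check matters too. In a simpler model (one third of accrual in a cohort at 30% risk, 8% elsewhere), the pooled rate passes in 69% of de-escalated trials if the rule fires at the second death. It passes in 57% if the rule is checked only at the seventh patient.

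**5. What a trigger shows.** The exact 95% confidence interval for 2/7 is 3.7% to 71.0%; for 5/39 it is 4.3% to 27.4%. With the same simulation structure, 40% IPF and one uniform risk in every group, at least one group triggers in about 43% of trials at a true risk of 8%, and in about 22% at 5%.

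**6. Would a per-group 15% limit be enough?** Not reliably. If more patients in the group receive the dose during the 6-month wait, 2/13 = 15.4% fails but 2/14 = 14.3% passes. A restriction tied to the trigger does not have this gap.

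**The case against.** **The pooling sentence is about survival.** This is correct. "All cohorts will be combined for this primary analysis" closes the survival power paragraph, treatment-related mortality is a secondary endpoint, and the denominator of the 15% limit is not given. A reader might infer that the protocol explicitly pools the mortality limit; it does not. Pooling is the natural reading because the limit belongs to the same single rule, and using all treated patients would still mix the groups. Only a within-group reading would avoid the problem, and no passage gives one.

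**No passage calls SABR worthwhile for a de-escalated group.** Also correct. The group is covered because the conclusion is worded for the whole population. The planned stratified presentation informs the reader but does not change the rule. Analysis detail may be left to a fuller document, but the rule and the scope of its conclusion are fixed in this one.

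**The two rules do not contradict each other.** A reader might infer that the trial would find a group unsafe and worthwhile at once. The documents do not support that. De-escalation is a precaution, not a finding that risk exceeds 15%: Table 6 has it firing 10% of the time at 8% risk, and 2/7 is very imprecise. For the same reason, a triggered group should not be reported as having failed the 15% limit.

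**The size depends on favourable inputs.** This stands in part. The 14% comes from the same sentence as the 33% and belongs in the range; it lowers the pass rate to about 26%. The cited difference has p = 0.092, the Background warns that true rates probably differ from the meta-analysis, and the Table 6 footnote treats risks above 30% as extremely unlikely. The gap in scope does not depend on these inputs; its frequency does.

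**Conclusion.** The concern holds as a point about the scope of the conclusion. The plan states one conclusion for the ILD population, gives no denominator for its mortality limit, and does not say what happens to the conclusion when a cohort or subtype has been taken off 50 Gy in 5 fractions. Replacing that group's later patients with patients from other groups makes a pooled pass easier.

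If IPF risk is 33%, de-escalation of IPF together with a pooled pass occurs in about 16-66% of trials as the risk elsewhere falls from 14% to 5%. Case mix, risks and immediate knowledge of outcomes are assumptions. These figures cover the mortality limit alone. The survival and grade 3 or 4 toxicity conditions must also be met, so the chance of an overall favourable conclusion in this situation cannot be larger and is probably smaller; it was not computed.

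This is a cheap improvement of moderate severity, not a flaw that must be repaired before the trial can be interpreted.

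**What to change.** Under Rationale for primary endpoint and study design and under Statistical design and sample size:

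- Name the population on which the two toxicity limits are judged.
- State that a favourable conclusion for 50 Gy in 5 fractions does not extend to any cohort or ILD subtype in which the de-escalation rule fired. Do not add that the group failed the 15% limit.
- Report treatment-related mortality at that dose by cohort and by subtype, with exact confidence intervals, next to the pooled figure.

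Tie the restriction to the trigger and not to the group's observed rate, because of the 2/14 case.

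The cost is a few sentences and one table. The downside is a narrower claim, sometimes for a group whose true risk is below 15%, since the rule also fires by chance. No dose, trigger or sample size changes.

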### Rationale for primary endpoint and study design

Important outcomes for patients with NSCLC and ILD include both toxicity and oncologic outcomes, and both were considered as possible primary endpoints.

Pulmonary toxicity was not chosen as a primary endpoint because it is very difficult to distinguish between radiation pneumonitis and ILD exacerbations. The patients included herein are expected to develop ILD exacerbations as part of the natural history of their ILD, and they are at risk of ILD-related death, which is difficult to distinguish from pneumonitis-related death. Erroneous attribution of ILD exacerbations to radiation could lead to the incorrect conclusion that the radiation dose should be lowered. In essence, the subjectivity of assigning the cause of toxicity should not be part of the primary outcome due to the risk of misattribution. However, pulmonary toxicity outcomes will be closely monitored in this trial.

Overall survival (OS) was chosen as the primary outcome as it objectively reflects the potential benefits of treatment (i.e. extended survival), the harms of treatment (grade 5 toxicity), and the natural history of the ILD disease process itself. Since the median survival of untreated Stage I NSCLC in inoperable patients is consistently reported as < 1 year (as noted above), we hypothesize that the use of SABR can achieve a median OS of > 1 year in patients with ILD. Though pulmonary toxicity is not to be the primary outcome in this trial, it will nevertheless be closely monitored to determine whether subsequently-enrolled patients will receive a deescalated radiation regimen.

SABR will be considered worthwhile if median OS is > 1 year with an acceptable risk of toxicity, defined as a grade 3 or 4 pulmonary toxicity rate of less than 35% and a risk of treatment-related death of less than 15%.

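### The survival criterion for calling SABR worthwhile is stated inconsistently: a one-sided 5% test in one place, simply OS above 1 year in the decision sentences

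*Protocol article*

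**What the plan says.** The Protocol article states the survival criterion in three forms.

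- **Statistical design and sample size, first paragraph.** SABR is indicated as worthwhile, given acceptable toxicity, if "median OS after SABR is statistically greater than a historical control of < 12 months".
- **Same section, second paragraph.** "A sample size of 39 patients provides >80% power to detect an OS improvement of >20% at 1 year", with 70% against 49% as the planning values, "using a one-sample, one sided binomial test at the 0.05 significance level" and "assuming 10% dropout or loss to follow-up before one year". All cohorts are pooled for this analysis.
- **Same section, last sentence.** "SABR will be considered worthwhile if OS is > 1 year", together with a grade 3 or 4 pulmonary toxicity risk below 35% and a treatment-related mortality risk below 15%. The section Rationale for primary endpoint and study design has a parallel sentence: "SABR will be considered worthwhile if median OS is > 1 year with an acceptable risk of toxicity", with the same two limits.

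Neither sentence that sets out the full three-part rule with its numerical limits mentions a test, an interval or a count. The one in the statistical section also omits the word median, so it names no statistic.

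**The concern.** This is an uncontrolled trial that ends in a go/no-go statement, so the sentence defining that statement should carry the error rate used to size the trial. As worded, a reader can apply either a test at one-sided 0.05 or a simple comparison of the observed median with 12 months. The two give different verdicts over a band of plausible results, and nothing in the decision sentences says which governs. If the choice is left until the data are in, the 5% error rate does not protect the primary conclusion.

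**Working it through.** **Inputs (all from Statistical design and sample size unless noted).** N = 39; null 1-year OS p0 = 0.49; alternative p1 = 0.70; one-sided alpha 0.05; 10% dropout, so 39 × 0.9 = 35.1, about 35 evaluable. From Rationale for a study: untreated 1-year mortality of 60–70%, i.e. 1-year OS of 30–40%.

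**1. The plan's own figure.** Normal approximation:

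n = [(1.645·√(0.49·0.51) + 0.842·√(0.70·0.30)) / 0.21]² = 33.1, so 34; 34/0.9 = 37.8, so 38.

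This is within one patient of 39, so the sample size reproduces.

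**2. What the stated test requires.** The cut-off is the smallest r with P(X ≥ r | n, 0.49) ≤ 0.05.

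| n | Cut-off | Error at 49% | Exact power at 70% |
|---|---|---|---|
| 39 | 25 (64.1%) | 0.0417 | 0.836 |
| 35 | 23 (65.7%) | 0.0347 | 0.773 |

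One fewer survivor at n = 39 (24) gives 0.080, which fails. With 35 evaluable, the normal approximation gives power 0.820 but the exact test gives 0.773.

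**3. What the decision sentence requires, read literally.** With complete 1-year follow-up, the observed median exceeds 12 months when more than half are alive at 12 months: 20 of 39, or 18 of 35. Results of 20 to 24 of 39 (20/39 = 51.3%, 24/39 = 61.5%) therefore satisfy the sentence and fail the test.

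**4. Error of the literal rule, survival condition only.**

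| True 1-year OS | P(X ≥ 20), n = 39 | P(X ≥ 18), n = 35 |
|---|---|---|
| 0.49 | 0.450 | 0.453 |
| 0.40 | 0.102 | 0.114 |
| 0.35 | 0.027 | 0.034 |

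Simulation agrees at 49%. With exponential survival, the sample median exceeds 12 months in 0.448 of trials at n = 39. The Kaplan-Meier 12-month estimate exceeds 0.5 in 0.454 with 10% dropout.

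**5. Null of 49% or 50%.** P(X ≥ 25 | 39, 0.50) = 0.054, so 25 of 39 rejects 49% but not 50%. P(X ≥ 23 | 35, 0.50) = 0.045, so 23 of 35 rejects both. At n = 39 a null of 50% needs 26 (error 0.027, power 0.740).

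**6. Toxicity limits as observed proportions of 39.** The largest passing counts are 5 for mortality (12.8%; 6 is 15.4%) and 13 for grade 3–4 pulmonary toxicity (33.3%; 14 is 35.9%). Their exact one-sided 95% upper bounds are 25.1% and 47.7%. With true rates exactly on the limits, the conditions pass with probability P(X ≤ 5 | 39, 0.15) = 0.459 and P(X ≤ 13 | 39, 0.35) = 0.487.

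**The case against.** The strongest reply is context. The statistical section has already said that worthwhile follows from a statistical demonstration, and it names the test. The closing sentence comes soon after and can be read as a summary that adds the numerical toxicity limits. No sentence says that point estimates are to be compared. On that reading the survival error is 3.5% to 4.2%, as intended. This stands, and it means the documents do not show that the trial has a 45% false-positive rate. The reply still requires the reader to infer the criterion and leaves open whether median OS or the 1-year proportion decides.

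Two further replies also stand in part:

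- **The 45% is conditional.** It needs the literal reading and a true rate of exactly 49%, and it covers one of three conditions. At the 30–40% survival implied by the protocol's own background figures it is 10% or less at n = 39. If both toxicity rates sat at their limits and the three conditions were independent (an assumption), the full verdict would be reached about 0.450 × 0.487 × 0.459 = 10% of the time.
- **Toxicity detail may be elsewhere.** Denominators and the time window for grade 3–4 toxicity may be in a full protocol or analysis plan not shown. The mortality window of 6 months is given under Secondary endpoints.

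A reader might also infer that the >80% power claim is wrong because three conditions must be met. The protocol makes that claim only for an OS improvement, so the inference is not supported.

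**Conclusion.** The survival criterion for the trial's conclusion is stated inconsistently and should be reconciled. Its size depends on the reading. Taken literally, the decision sentences accept 20 to 24 of 39 survivors where the exact test needs 25, and at a true 49% the survival condition alone is met 45% of the time instead of 4.2%. Taken as shorthand, the error is as planned. The calculations treat 1-year status as binary with either 39 or 35 patients evaluable.

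It would go too far to say that the rule contradicts the 5% test outright. It would also go too far to say that passing the test can never support a median above 12 months: that gap appears at 25 of 39 but not at 23 of 35, and the protocol itself represents its historical control by 49%. What the toxicity limits lack in this document is any statement of precision. Counts that just pass are compatible with true rates well above the limits.

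**What to change.** In Rationale for primary endpoint and study design and in Statistical design and sample size:

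- State that the OS condition is met only if the one-sided 0.05 binomial test of 1-year OS rejects 49%: at least 25 of 39, or 23 of 35 evaluable. Note that exact power with 35 evaluable is 77.3%, not above 80%.
- If the intended claim is that median OS exceeds 12 months, set the null at 50%. At n = 39 this raises the cut-off to 26 and lowers exact power to 74.0%; at 35 evaluable the cut-off stays at 23.
- Report the two toxicity rates with exact one-sided upper bounds beside the 35% and 15% limits.
- State that the >80% power refers to the OS test alone, not to the three-part verdict.

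The cost is wording, plus a survival condition stricter than the literal rule. No extra patients are needed to make the statements consistent, although the power figure has to be given less favourably if 35 are evaluable.
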